## Methods

### Primary objective

The primary objective of this trial is the evaluation of safety and feasibility of neoadjuvant hypofractionated irradiation in patients with extremity sarcoma using ions (protons or carbon ions) in raster scan technique. The primary endpoint is defined as the rate of wound healing disorders from beginning of radiotherapy to maximum 120 days after the planned tumor resection or discontinuation for any reason related to the treatment.

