### Toxicity, safety, and quality of life

Adverse events and toxicity will be reported according to International Common Terminology Criteria for Adverse Events (CTCAE) version 5.0 system. The results of clinical examinations as well as imaging studies (MRI or CT) will be included. Each patient will pass a baseline clinical examination after enrollment. Patients are monitored continuously during treatment, acute adverse events will be documented weekly as well as at the end of treatment. MRI of the according extremity will be planned 3 weeks and the resection 4–6 weeks after the end of radiotherapy. The first clinical follow-up presentation is 6 weeks after resection. Hereinafter all follow-ups include imaging studies and are performed 3, 6, 9, and 12 months after the tumor resection (Table 1). The criteria for feasibility and safety are fulfilled, if the rate of wound healing complications within 120 days after surgery is below 15% and if the therapy was not canceled, unless the reason for canceling is clearly not treatment related.

**Table 1 Tab1:** Time flow of procedures and examinations

	Study inclusion	Prior to RT	During RT	At the end of RT	3 wk. after RT	OP: 4-6 wk. after RT	6 wk. after RT	3 mo. after OP	6 mo. after OP	9 mo. after OP	12 mo. after OP
Inclusion and exclusion criteria	x										
Informed consent	x										
Medical history	x		x	x	x		x	x	x	x	x
Evaluation of symptoms and toxicity	x		x	x	x		x	x	x	x	x
Radiotherapy			x								
Resection						x					
MRI extremities		x			x			x	x	x	x
CT Thorax		x						x	x	x	x
Quality of life (QLQ-C30)		x			x			x			x

Quality of life (QoL) will be assessed by EORTC QLQ-C30 questionnaires. Repetitive completion of the forms is scheduled before treatment, 3 weeks after the end of radiotherapy, 6 months after surgery, and at the end of the study 12 months after surgery. Statistical analysis will be performed after complete acquisition of data. Changes in QoL before and after radiotherapy and before and after surgery will be determined. The two arms of the study will be compared after the end of radiation and at the end of the whole study.

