### Statistical methods

This study is performed to deliver basic data for the neoadjuvant hypofractionated carbon ion or proton radiation treatment of patients with extremity soft tissue sarcoma by providing safety and toxicity data for the here presented treatment regimen. The framework of the safety and feasibility considerations is the current standard neoadjuvant normofractionated photon radiotherapy; it is considered as the historical cohort which served for the planning of this pilot study. The randomization will be performed as block randomization at a ratio of 1:1 aiming at equal group sizes by using a web-based randomization tool (randomizer.at).

Due to the pilot character of the trial, all analyses are performed descriptively and the results are to be interpreted accordingly. The primary endpoint is assessed separately in each of the two treatment groups by applying an optimal adaptive two-stage phase II-design with one interim analysis according to Kunzmann and Kieser [19]. This design is an adaptive variant of Simon’s design [20], where the sample size of stage two is chosen optimally based on the results of the interim analysis. It offers the possibility to prematurely terminate the study due to futility or early success at the timepoint of the interim analysis or allows data-driven recalculation of sample size for the second part of the study while adhering to the specified Type I and Type II error rates. The randomization will be performed as block randomization at a ratio of 1:1. After the interim analysis, dependent on the results, different sample sizes in both treatment arms may be required and the randomization ratio would then be adjusted accordingly. Under the null hypothesis, we would expect in both groups wound complications or dicontinuations to occur in ≥35% of the treated patients within 120 days after surgery, so the expected probability of patients with no wound complications and no discontinuation would be π ≤ 65% for both protons as well as carbon ions. Under the alternative hypothesis, we would expect less than 15% of the patients to have wound complications or discontinue therapy within 120 days after surgery with π ≥ 85% being the rate of patients without wound complications or discontinuation within 120 days after surgery.

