Given these probabilities of success for the alternative and null hypothesis for the protons and carbon ion group, a statistical power of 1-β = 0.80 and a one-sided Type I error rate α = 0.05 for each of the two comparisons, the expected sample size under the null hypothesis is 25.59 and under the alternative hypothesis it amounts to 29.97; the maximum sample size in this design is 52. The interim analysis is performed when the data of 21 patients are available and therefore this is the minimum sample size. The recalculated sample sizes for stage 2 in both treatment arms depend on the patient number with a treatment success (no wound complications and no discontinuation). These values as well as the boundaries for early stopping and the decision boundaries after stage two are calculated according to Kunzmann and Kieser [19] with program code supplied by the authors. The estimation of success rates in both study arms is performed by calculation of point estimators [21] and calculation of two-sided 95%-Clopper-Pearson-type confidence intervals that take the adaptive two-stage design into account [22].

Analysis of the secondary time-to-event endpoints LPFS, DFS, and OS will be performed by the Kaplan–Meier method, patients without event will be censored. The treatment groups are compared using the logrank test. Quality of life will be measured by the EORTC-QLQ30 questionnaire and assessed by presentation of mean, standard deviation, median, minimum, and maximum as well as application of a two-sample t test. For the secondary endpoint local control, absolute and relative frequencies are calculated for each treatment group together with two-sided 95% Agresti–Coull confidence intervals, and an unconditional fourfold table test will be applied for treatment group comparison. Adverse and serious adverse events will be listed, and absolute and relative frequencies will be calculated.

The primary analysis for the primary and secondary endpoints is based on the intention-to-treat set including all study patients fulfilling the inclusion/exclusion criteria and having been treated for at least 1 week. Additionally, a per-protocol analysis is performed as sensitivity analysis which is based on all patients who have received the treatment as planned and for whom the relevant data is available. Safety endpoints are evaluated for all study patients for which the treatment has started.

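### The per-protocol sensitivity set excludes the treatment-related discontinuations that the primary endpoint counts as failures, so it cannot test feasibility

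*Protocol article*

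**What the plan says.** All references are to the Methods of the protocol article.

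- **Endpoint.** Primary objective names safety and feasibility as the aim. Its endpoint covers wound healing disorders up to 120 days after the planned resection, or "discontinuation for any reason related to the treatment".
- **Feasibility criterion.** Toxicity, safety, and quality of life requires a wound complication rate below 15% and is met only "if the therapy was not canceled, unless the reason for canceling is clearly not treatment related".
- **Design.** Statistical methods sets the null hypothesis as wound "complications or dicontinuations to occur in ≥35% of the treated patients", which is a success rate of at most 65%. The alternative is a success rate of at least 85%. The stage-two sample size depends on the number of patients with a "treatment success (no wound complications and no discontinuation").
- **Primary analysis set.** This is an "intention-to-treat set including all study patients fulfilling the inclusion/exclusion criteria and having been treated for at least 1 week".
- **Sensitivity analysis.** The article states that "a per-protocol analysis is performed as sensitivity analysis which is based on all patients who have received the treatment as planned"; their endpoint data must also be at hand. No other sensitivity analysis is named.

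**The concern.** A sensitivity analysis earns its place by being able to disagree with the primary result. Here, completing the treatment is part of the outcome and is also the condition for entering the set. A patient who stops irradiation for a treatment-related reason has not received it as planned, and the article makes no exception that keeps such a patient in as a failure. On the discontinuation component, the per-protocol analysis is therefore nearly blind by definition.

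Discontinuation is the feasibility signal in this endpoint. If the per-protocol rate agreed with the primary rate or exceeded it, a reader would probably take that as robustness, although part of the agreement would come from how the set is defined.

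**Working it through.** **Inputs.** The success rates π = 0.65 (null) and π = 0.85 (alternative) and the maximum sample size of 52 come from Statistical methods. The share d of patients in the primary set who fail through a treatment-related discontinuation is not given, so 2%, 5% and 10% are assumed. The article gives no per-protocol rate to reproduce.

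**Step 1: only treatment-related discontinuations are removed.** All of those removed are failures. The numerator stays at π and the denominator falls to 1−d, so the per-protocol rate is π/(1−d), which exceeds π for any d > 0.

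| assumed d | π = 0.65 | π = 0.85 |
|---|---|---|
| 2% | 0.65/0.98 = 66.3% | 0.85/0.98 = 86.7% |
| 5% | 0.65/0.95 = 68.4% | 0.85/0.95 = 89.5% |
| 10% | 0.65/0.90 = 72.2% | 0.85/0.90 = 94.4% |

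In counts, take 34 successes among 52 patients, which is 65.4%. If 5 of the 18 failures are treatment-related discontinuations, the per-protocol rate is 34/47 = 72.3%, although no additional patient has done well.

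**Step 2: other patients are removed as well.** The set also drops patients with unrelated deviations or without relevant data, and some of these may be successes. Let u be their share and s the success rate among them. The per-protocol rate is then (π − u·s)/(1 − d − u). At π = 0.65 and d = 5%:

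- u = 5%, s = 50%: (0.65 − 0.025)/0.90 = 69.4%
- u = 5%, s = 100%: (0.65 − 0.05)/0.90 = 66.7%
- u = 10%, s = 100%: (0.65 − 0.10)/0.85 = 64.7%

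The shift is upward whenever u(s − π) < π·d. With s = 100% and d = 5%, it vanishes at u = 0.65 × 0.05/0.35 = 9.3%. Cancelling it would thus need about 9% of patients to be dropped for other reasons, every one of them a success.

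**Step 3: the proposed rule.** If treatment-related discontinuations stay in as failures, d no longer leaves the denominator. With no other exclusions the rate remains at 65% or 85%.

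**Step 4: whether the primary set fills the gap.** It does so only in part. Discontinuations after the first week remain there as failures, but the one-week minimum removes earlier ones. At 5–6 fractions per week, the first week covers 5/13 = 38% to 6/13 = 46% of the 13 fractions. Neither set therefore counts every treatment-related discontinuation.

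**The case against.** **It is only a sensitivity analysis.** This stands as a limit on the consequences. The primary analysis rests on the other set, all analyses are called descriptive, and discontinuations after week 1 count as failures in the primary result. Safety endpoints are evaluated in everyone who started treatment. An attentive reader could compare the two sets and see what was dropped.

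**Per-protocol sets usually exclude non-completers, and the full protocol or analysis plan may say more.** The convention is tolerable when completion is not the outcome, but here it is part of it. The point does not rest on silence: the article states both the endpoint and the set, and the two collide as written.

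**The size is unknown.** This stands. The article gives no discontinuation rate, and its 35% null figure equals the wound complication rate that the Background cites for preoperative radiotherapy. The upper end of the assumed range has no anchor in the text.

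**Stronger readings that the article does not support.** A reader might infer that the per-protocol analysis raises the chance of a false positive decision, or misuses the two-stage boundaries. The article does not say that those boundaries are applied to the per-protocol set. The design turns on the number of successes, and removing failures from an enrolled cohort leaves that number unchanged. A higher rejection probability would need full-sized sets drawn at the inflated rate, that is, replacement of discontinued patients, and the article describes no such replacement. A reader might also infer that the overall per-protocol rate must be too high. That is exact only for the discontinuation component, because other exclusions can offset it, as step 2 shows.

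**Conclusion.** The point holds in a limited form. As written, the only named sensitivity set excludes patients for an event that the primary endpoint counts as failure, so it cannot test the feasibility component. With only those removals, a true 65% would read as 66.3% to 72.2% for assumed discontinuation shares of 2% to 10%. The net shift depends on the remaining exclusions and would usually, but not necessarily, be upward.

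This rests on the plain reading that a patient who stops irradiation early for a treatment-related reason has not received the treatment as planned. The primary conclusion, the stage decisions and the error rates of the design are not affected. The definition should still be corrected, because it builds a bias into the result instead of merely leaving a detail open.

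**What to change.** 1. Reword the per-protocol definition so that every treatment-related discontinuation stays in the set as a failure, and exclusions are limited to deviations that are not themselves endpoint events.
2. Add one sensitivity analysis of all randomised patients, by arm, with treatment-related discontinuation and missing endpoint status counted as failure. This leans the conservative way and also brings back the first-week discontinuations that the one-week minimum removes from the so-called intention-to-treat set.

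The cost is a short change of wording and one extra table. The per-protocol rate may look less favourable, and the all-randomised rate will be pessimistic if much endpoint status is missing, so it should be read as a lower bound beside the primary estimate. Sample size, randomisation and treatment do not change.

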### Data safety monitoring board

A Data and Safety Monitoring Board (DSMB) is composed of independent experts. The DSMB will monitor the recruitment, the reported (serious) adverse events as well as the quality of data. The goal is to ensure that the study is executed according to current standards of good clinical praxis with focus on the safety interest of the patients. The DSMB will give the principal investigator (PI) recommendations regarding trial modification, continuation, or premature termination.

### Regular study end

The estimated period of patient accrual is 2 years. The regular end of treatment for the individual patient is 2 to 3 weeks after beginning of radiation therapy (13 fractions, 5–6 fractions per week). The regular study end for each patient is after 12 months after surgery. Patients will be then monitored by regular follow-ups according the current guidelines.

### Premature study termination

Reasons for premature termination of the entire study are:i.Unacceptable risks or toxicities (assessment by DSMB)ii.One toxicity of grade 5 or two consecutive grade 4 toxicities or five consecutive grade 3 toxicities unequivocally associated with the study therapy. The DSMB assesses and concludes whether a toxicity equal or higher than grade 3 is associated with the study treatment.iii.New scientific findings incompatible with the study treatment.

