## Background

Soft tissue sarcomas (STS) collectively account for approximately 1% of all adult malignancies [1]. There are more than 50 subtypes, while pleomorphic sarcoma, liposarcoma, leiomyosarcoma, synovial sarcoma, and malignant peripheral nerve sheath tumor account for 75% of STS [2]. With 43% the most common localization for STS are the extremities. Limb sparing wide resection in combination with radiotherapy (RT) is the current standard of care for high grade soft tissue sarcomas of the extremities [3]. Especially patients with G2/G3 sarcomas profit from the combination of RT and surgery [4]. Well-differentiated sarcomas (G1) receive no subsequent treatment after total resection (R0). Compared to amputation limb sparing resection with adjuvant RT shows similar overall survival (OS) und disease free survival (DFS) rates with a high local tumor control (LC) according to prospective studies [4–6] and a recent meta-analysis [7]. The status of postoperative resection margins is the most important prognostic factor contributing to LC with local recurrence (LR) being up to 3.76 times more likely in patients with positive compared to negative resection margins [8]. The sequence of surgery and RT is widely discussed by the radiation oncologists and surgeons. The main advantages of neoadjuvant (preoperative) radiotherapy are the smaller treatment target volumes and reduced prescribed radiation doses of 50 Gy vs. 66 Gy in 2 Gy single doses in the postoperative setting. Both preoperative and postoperative RT show a similar improvement in LC in prospective studies [4, 9–12]. In a recent retrospective study preoperative RT was predictive for R0 resection [13]. However, a greater incidence of acute wound complications was associated with preoperative compared to postoperative RT (35% vs.17%). Late-treatment–related side effects were more frequent in patients receiving postoperative RT, which could be explained by the higher RT dose and the larger treatment volume [10, 14]. The special physical and biological properties of protons and carbon ions lead to a superior dose distribution [15, 16]. This allows a better sparing of the surrounding tissue including the skin, muscles, joints, bones and subcutaneous fatty tissue, potentially reducing acute postoperative wound complications or late treatment related toxicities like fibrosis, joint stiffness, bone fracture or edema. Carbon ions are furthermore superior to protons based on their enhanced biological effectivity, which qualifies those for the treatment of tumors of low radiosensitivity as sarcomas. The standard neoadjuvant normofractionated radiotherapy consists of 25 fractions with 2-Gy single dose over 5 weeks; the special properties of particles allow hypofractionation resulting in a reduced treatment duration of less than 3 weeks.

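### Counted as successive patients across the whole study, the trigger of five consecutive grade 3 toxicities would seldom fire, even with one highly toxic arm; limits on cumulative counts per arm would do better

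*Protocol article*

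**What the plan says.** The Protocol article, section Premature study termination, opens its list with "Reasons for premature termination of the entire study are". Clause ii of that list is "One toxicity of grade 5 or two consecutive grade 4 toxicities or five consecutive grade 3 toxicities unequivocally associated with the study therapy". It continues: "The DSMB assesses and concludes whether a toxicity equal or higher than grade 3 is associated with the study treatment". Clause i is a separate, discretionary stop for risks or toxicities that the DSMB judges unacceptable.

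The clause fixes the grades, the counts, the word 'consecutive' and the consequence. It does not say whether patients or reports are counted, or whether a run is counted per arm or across both arms.

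Three statements under Statistical methods bear on how the clause performs. On allocation: "The randomization will be performed as block randomization at a ratio of 1:1". On timing: "The interim analysis is performed when the data of 21 patients are available and therefore this is the minimum sample size". The primary endpoint is assessed separately in each arm, and the alternative hypothesis sets the acceptable level: "we would expect less than 15% of the patients to have wound complications or discontinue therapy within 120 days after surgery".

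**The concern.** Safety and feasibility are the primary objective, and clause ii is the numeric toxicity trigger in force between formal looks. A run rule forgets everything before the last patient without an event, so a high but not overwhelming rate rarely produces five in a row. If the run is also counted across both arms, patients from a well-tolerated modality break up the events of a poorly tolerated one. The trial treats two modalities that may differ in toxicity, and it judges them separately on the primary endpoint, so this is the situation that a toxicity trigger should detect. At stake is whether clause ii adds useful protection before the interim data mature, which includes the follow-up to 120 days after surgery.

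**Working it through.** The article states no stop probability for clause ii, so there is no figure of its own to reproduce.

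**Inputs**
- Run lengths: five for grade 3, two for grade 4 (clause ii).
- 21 patients at the interim and a maximum of 52 (Statistical methods). Both are read as per arm, giving 42 and 104 in total.
- Acceptable failure rate 15% (Statistical methods).
- Assumptions: independent patients; at most one counted event per patient; block size 4 or 6; 50% against 5% as an illustration of one toxic arm. The article gives no grade 3 rate, so rates are varied. Treating every failure as an attributed grade 3 toxicity is an upper bound. On the patient reading it favours the rule.

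**1. Five successive patients, one study-wide sequence**

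Let F(n) be the chance of a run of five by patient n. Then F(n) = 0 for n < 5, F(5) = p^5, and F(n) = F(n−1) + [1 − F(n−6)](1−p)p^5.

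At p = 0.35, p^5 = 0.00525 and (1−p)p^5 = 0.00341. Ignoring the bracket gives an upper bound at n = 42 of 0.00525 + 37 × 0.00341 = 0.131; the exact recursion gives 0.125.

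| True rate, both arms | F(42) |
|---|---|
| 15% | 0.25% |
| 35% | 12.5% |
| 50% | 49% |

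The 35% is the wound-complication rate cited for preoperative photon treatment. It is used here only as a point on the curve, not as a harm threshold.

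**2. One toxic arm, 50% against 5%, 42 patients**

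With blocks of 4, each block holds two patients per arm, so at most four successive patients can come from the same arm. Every window of five therefore contains a low-rate patient, and its chance of being all events is at most 0.5^4 × 0.05 = 0.3%. The same recursion, averaged over all permuted blocks, gives 0.9% (blocks of 4) and 1.5% (blocks of 6). A run counted only within the toxic arm, n = 21, gives 26%.

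**3. Five successive reports**

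If other grades do not break the run, the rule becomes P(X ≥ 5) with X ~ Binomial(N, p), a plain count.

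| Attributed grade 3 rate | N = 42 | N = 104 |
|---|---|---|
| 15% (all failures at the acceptable rate) | 78% | 99.97% |
| 10% | 41% | 98% |
| 7.5% (half of them) | 20% | 90% |
| 5% | 6% | 60% |
| 3.75% (a quarter) | 2% | 35% |

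If grade 4 reports occur in 2% of patients and break the run, the 15% row at N = 42 falls to 60%.

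**4. Grade 4 part, two successive patients, 42 patients**

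The chance is 31.5% at a 10% rate and 76% at 20%. This part is less affected.

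**5. A cumulative per-arm limit, for illustration only**

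Pause the arm at 6 affected within its first 7 treated, 8 within 14, or 10 within 21, checked after each patient. At a true rate of 50% in that arm:

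| Patients treated in the arm | Cumulative limit | Run of five within the arm |
|---|---|---|
| 7 | 6% | 6% |
| 14 | 40% | 17% |
| 21 | 68% | 26% |

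At 15% the cumulative limit pauses an arm under 0.1% of the time by patient 21 (0.07%).

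**The case against.** The best reply has four parts.

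- **Condensation.** The article condenses a full protocol (Version 1.2) that is not shown. The counting unit and the arm may be defined there or in a DSMB charter. This stands as far as it goes: an undefined word alone would not be a finding. But the article prints the number five and the word 'consecutive', and a definition as successive patients, study-wide, would confirm the insensitivity.
- **Unknown rate.** No grade 3 rate is given. The 15% covers wound complications and discontinuations generally, while clause ii counts only events that the DSMB finds unequivocally related to treatment. This stands against the report reading. A reader might infer from the 78% and 99.97% that the clause would probably stop an acceptable trial. The documents do not support that: those figures treat every failure as an attributed grade 3 toxicity and reduce 'consecutive' to a plain count, and 99.97% also needs both arms at the maximum size. If lower-grade reports break the run, this reading becomes insensitive as well.
- **Other safeguards.** The DSMB monitors adverse events and may recommend modification or termination, and clause i lets it stop the trial on judgement. The interim analysis tests each arm with a futility stop. Its boundary is not shown, but if it lay at 12 to 14 successes or fewer out of 21, an arm failing at 50% would stop 81% to 96% of the time. This stands, apart from the wait for 120-day data.
- **Flattering illustration.** The 68% is reached only at patient 21, when the interim falls due. This stands: at patient 7 there is no gain over a within-arm run, and at patient 14 the comparison is 40% against 17%.

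**Conclusion.** The concern holds in a limited form. As a run of successive patients across the study, the grade 3 part of clause ii is a weak detector: 12.5% at a 35% rate, 49% at 50%, and 0.9–1.5% when one arm has 50% and the other 5%. These figures assume independent patients, 21 per arm and, for the last, blocks of 4 or 6. Pooled counting is itself a reading; the words 'entire study' settle what is stopped, not how events are counted. Over-firing under the report reading is conditional on an attributed grade 3 rate near 10–15% or on long recruitment.

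A reader might also infer that the trial has no working protection against a toxic arm. The text does not support that: clause i, ongoing DSMB monitoring and the per-arm interim analysis all remain, the grade 5 part is sound, and the grade 4 part is less affected. The point should be fixed, at moderate importance, as a cheap improvement.

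**What to change.** In clause ii, replace 'consecutive' for grades 3 and 4 with the cumulative number of affected patients out of those treated, counted separately in each arm. Set limits that rise with the number treated, and let a crossed limit pause one arm for DSMB review.

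The DSMB should choose the limits from a table of stop probabilities by number treated, including before patient 21, over plausible attributed grade 3 and grade 4 rates. They should not be set against the 35% standard-of-care wound-complication rate. The limits in step 5 of the working show what such a table looks like and are not a proposal. Keep the grade 5 part, the DSMB's attribution and clause i unchanged.

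The cost is amendment wording and a short table, with no extra patients or procedures. The downside is that an arm may be paused somewhat earlier than now.
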